### Allocation concealment and blinding

The supplement and placebo are provided by Gencor Pacific Ltd and will be provided in white opaque identical containers labelled either ‘A’ or ‘B’. The contents of each container will be provided in a sealed envelope that will only be made available to the researcher responsible for the sequence allocation who is not associated with the study. The researchers responsible for data collection and participant management will both be blinded to the groups and will not be made aware of the group allocation until after the data analysis.

### Methods: data collection, management and, analysis

#### Data management and monitoring

Research assistants that are blinded to the supplement allocation will be trained on how to collect data. Data for body composition and exercise testing will be collected at the same location throughout the study. These data will be collected electronically, and research assistants will also backup electronic data using de-identified, participant coded data collection sheets. The electronic data is stored on password protected computers and the data sheets are stored in a locked filing cabinet. All research data collected will be transferred to an excel worksheet on password protected servers. While data is being collected, all data will be checked for omissions or errors by the project manager who will maintain a data diary of any issues that arise with the data. The data then will be checked again by the principal investigator (PI) and statistician prior to any analysis. The information collected from this study will be kept until the end of the project and then placed in archives for a minimum of 5 years from the final publication of the findings.

The CMJ, IMTP and bench throw will be taken in triplicate. A fourth measure may be taken if two of the measurements are not within ~ 10% of each other. Participants will have regular contact (2xdays/week) with the researchers and receive check-ins if they have missed sessions. Participants will have the opportunity to re-schedule missed sessions during the same week of training.

Any adverse effects recorded by participants will be reported directly to the PI. The PI will directly report adverse effects to the Therapeutic Goods Administration (TGA) in the Department of Health and Age Care, Australia. In the unlikely event of severe adverse reactions, the PI will make the final decision to terminate the trial.

#### Statistical methods

A primary analysis of intention to treat (ITT) will be conducted of all the participants that have completed the trial. A secondary, per-protocol analysis will be carried out to include only participants that attend ≥ 80% of their resistance training and consumed ≥ 80% of their supplement over the course of the study. Between-group comparisons will be made using linear models adjusting for baseline outcome level and stratification factors sex and SMI (low/high). Outcome variables will be log-transformed where necessary to satisfy parametric assumptions. All tests will be two-tailed with statistical significance set at p < 0.05. Multiple imputation by chained equations will be used to handle missing data.

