### Interventions

#### Supplements

Eligible participants will be asked to maintain their usual dietary intake and current exercise habits, abstain from using any pain medication, and sports supplements that are not provided during the course of the study. The intervention groups will be provided capsules of PEA (350 mg/day as 2 × 175 mg Levagen + ® capsules), or identical matching placebo capsules (in colour and weight) containing maltodextrin (2 × 175 mg capsules), which will be taken orally (swallowed) for 8-weeks. On training days, participants will be instructed to take 1 × capsule 45 - 60 min prior to exercise with their standardised meal (388 kcals, 45 g CHO, 21 g PRO, 13 g FAT) and 1 × capsule in the evening 60 min prior to sleep [32]. The supplement taken prior to exercise is provided based on the time to peak blood concentrations of PEA (~ 45–60 min) [34]. On non-training days, participants will be asked to consume 1 × capsule with their morning meal and 1 × capsule pre-sleep, 60-min prior as per training days. The dosage of the supplement within this study is well below previous studies that have shown dosages of up to 1,200 mg/day have no harmful effects [35]. In the rare case that a participant may experience undesirable side effects, the blind will be broken, and participants will be referred to a local general practitioner and they may withdraw from the study.

The trial products will be supplied by Gencor Pacific (Lantau Island, Hong Kong) and manufactured by Pharmako Biotechnologies (Sydney, Australia). Compliance with dosing at home will be assessed by pill count and a tracker sheet at the end of the study.

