### Sample size

It has been calculated that a sample size of 42 participants (21 per group) will provide 80% power, for α = 0.05, to detect a 2% difference between groups in percentage lean mass change [assumed SD = 2.2% based on data from [42] to detect a significant change in lean muscle mass. To allow for an ~ 20% dropout rate, we will aim to recruit 52 participants in total. As proof of principle, a study by Lilja et al. [19] demonstrated a significant difference in muscle mass and strength between participants treated with NSAIDs vs placebo after 8 weeks of resistance training with a participant pool of 35 participants. Sample size calculations were performed in Stata/SE 16.1 (StataCorp, TX) using the *power two means* command.

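### The primary analysis is called intention to treat but is limited to participants who completed the trial, so no planned analysis covers everyone randomised

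*Protocol article*

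**What the plan says.** All quotations are from the protocol article.

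- **Primary population** (Statistical methods): "A primary analysis of intention to treat (ITT) will be conducted of all the participants that have completed the trial".
- **Secondary population** (same section): "A secondary, per-protocol analysis will be carried out to include only participants that attend" at least 80% of training and take at least 80% of the supplement.
- **Model** (same section): "Between-group comparisons will be made using linear models adjusting for baseline outcome level and stratification factors sex and SMI (low/high").
- **Missing data** (same section): "Multiple imputation by chained equations will be used to handle missing data". The population and the variables to be imputed are not named.
- **Expected loss** (Sample size): "a sample size of 42 participants (21 per group) will provide 80% power". With an allowance of about 20% for dropout, "we will aim to recruit 52 participants in total".
- **Timing of the primary outcomes** (Lean body mass): DXA and pQCT are taken at weeks 0, 1 and 11, so week 11 is the only measurement after baseline.
- **A route to withdrawal** (Supplements): in what the article calls the rare case of undesirable side effects, the participant is unblinded and referred, and "they may withdraw from the study".

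**The concern.** Intention to treat means that everyone randomised is analysed in the group to which they were allocated. The sentence in the article uses that name but selects people by an event that occurs after randomisation. Randomisation makes the two groups comparable as randomised; it does not guarantee that those who finish are comparable. If the reasons for leaving differ by arm, the completers' difference mixes the effect of PEA with the selection of who stayed.

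The per-protocol set does not fill the gap, because it is narrower still. Every analysis that the article defines therefore leaves out the withdrawals. The result would also be published under a label that tells readers it has a protection it lacks.

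The imputation sentence makes the plan ambiguous. Withdrawal is the main way to lose a week-11 scan. If withdrawals are outside the analysis set, the imputation hardly touches the primary outcomes; if they are inside it, the first sentence is wrong. Two analysts following the same section could analyse about 42 or 52 people.

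**Working it through.** **1. The plan's own figures.** Inputs from Sample size: difference 2 points, SD 2.2, two-sided alpha 0.05, equal groups. Power of the two-sample t test comes from the noncentral t distribution with 2n − 2 degrees of freedom and noncentrality 2 / (2.2 × √(2/n)).

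- n = 20 per arm: 79.997%, just under 80%.
- n = 21 per arm: 82.0%.

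So 21 per arm, 42 in total, reproduces. For dropout, 42 / 0.80 = 52.5, and the plan's 52 matches its allowance of about 20%. The sample size is not at issue.

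**2. How many people the definition can exclude.** 52 − 42 = 10, and 10 / 52 = 19.2%. This is a planning allowance, not a forecast.

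**3. Bias when dropout rates differ by arm.** Suppose that in both arms those who leave gain D points less than those who stay, and that dropout is d₁ on PEA and d₀ on placebo. Each arm's mean over all randomised is its completer mean minus d × D. The completers' difference is therefore too large by (d₁ − d₀) × D. The splits and gaps below are assumptions; the article gives none.

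| Dropout, PEA vs placebo | D = 1 point | D = 2.2 points (1 SD) |
|---|---|---|
| 20% vs 20% | 0 | 0 |
| 25% vs 15% | 0.10 | 0.22 |
| 30% vs 10% | 0.20 | 0.44 |

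Against the 2-point target, the largest entry is 0.44 / 2 = 22%. If PEA losses are the more numerous but those who leave are the better responders, the sign reverses.

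**4. Bias when rates are equal but reasons differ.** If 20% leave in each arm, placebo losses are random, and PEA leavers gained 2.2 points less than those who stayed, the bias is 0.20 × 2.2 = 0.44 points.

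A simulation of the same idea used 26 per arm, 5 lost per arm, SD 2.2 and a true effect of zero. The chance of loss on PEA was weighted by exp(−k × change in SD units).

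| Loss mechanism (assumed) | Analysis | Bias (points) | Type I error |
|---|---|---|---|
| PEA k = 0.9, placebo random | completers | 0.37 | about 9% |
| PEA k = 0.45, placebo random | completers | 0.20 | about 6% |
| k = 0.9 in both arms | completers | about 0 | about 6% |
| PEA k = 0.9, placebo random | all 52, multiple imputation with arm in the model | 0.37 | 8.6% |

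The last row matters for the fix. When loss depends on the unseen outcome itself, imputation under missing at random reproduces the completers' bias. Baseline values and attendance would help only as far as they predict the lost change, and there is no interim scan to inform it.

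**5. Power with all 52 analysed.** At 26 per arm and the full 2-point effect, power is at most 89.5%, if no information is lost to missing data. If the 20% who leave gain no benefit, the effect over all randomised is 2 × 0.8 = 1.6 points, and power is 73.0%, on the same assumption about information.

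**The case against.** The strongest defence is that the sentence is loosely worded. It may mean completers whatever their adherence, to set them apart from the per-protocol set, and the imputation sentence may show that withdrawals were meant to be included. That intention is plausible, but the text does not state it: no section defines a set of all randomised participants.

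Several further objections stand and limit the point:

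- **Conflict with the imputation.** A reader might infer that the two sentences flatly contradict each other. They do not. Imputation can still fill completers' gaps in questionnaires, actigraphy, assays or an unusable scan. The tension is confined to the primary outcomes, where it is left with almost nothing to do.
- **Treatment-related withdrawal.** The article calls side effects rare and says the dose is well below doses reported as harmless. Blinding and identical training also work against differential loss. The Supplements text shows that such withdrawal is possible, not that it would drive the dropout.
- **The count of 10.** The article has retention measures: a gift card on completion, check-ins and rescheduling of missed sessions. Actual loss may be smaller.
- **The one-sided scenario.** Nothing in the article supports poor responders leaving PEA while placebo losses are random.

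**Conclusion.** The point holds. The stated primary population is a completers set under an intention-to-treat label, and no planned analysis covers all randomised participants. This is a rule the article states wrongly, not a detail left to an analysis plan.

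Its size is uncertain. Up to about 10 of 52 participants are affected if the full dropout allowance is used. The bias is about 0 if losses are alike in both arms and about 0.1 to 0.4 points if they differ by arm in the ways assumed above.

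A reader might infer that the trial faces a type I error near 9%, or that including everyone with imputation would cure it. The documents support neither. The 9% arises only under one assumed, one-sided, outcome-dependent mechanism, and under that mechanism imputation left the error at 8.6%. The case for change is that the label and the population disagree, and that the plan should not discard randomised participants by design.

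**What to change.** Reword the primary analysis before unblinding, along these lines: the primary analysis includes all randomised participants in the group to which they were allocated, whatever their completion, attendance or supplement intake. Then:

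1. Apply the planned multiple imputation to missing week-11 values, with arm, week-0 and week-1 values, sex, SMI and attendance in the imputation model. Attendance, observed after randomisation, belongs in the imputation model only and not in the analysis model.
2. Add a sensitivity analysis for data not missing at random, such as a delta adjustment by arm. Shifting imputed PEA values by 1 to 2.2 points with 20% missing moves the estimate by 0.20 × 1 = 0.20 to 0.20 × 2.2 = 0.44 points, which shows how robust the conclusion is.
3. Keep the completers analysis, named as such, as a sensitivity analysis next to the per-protocol analysis.

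The cost is a change of wording and slightly more analysis work. The variables are already collected, and the sample size of 42 evaluable and 52 recruited need not change on this account. A possible consequence is a smaller estimated effect if those who leave benefit less (step 5 of the working).

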### Objectives

The primary aim of this study is to investigate the effects of daily PEA supplementation (Levagen + ®) during an 8-week period of resistance training on pre- to post-intervention changes in total body and regional lean body mass (e.g., mid-thigh) compared with a placebo condition. Our secondary aims are to explore the effects of PEA supplementation on changes in strength, power, sleep, subjective wellbeing, and pain associated with resistance training and menstruation.

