### Primary outcomes

#### Lean body mass

The primary outcomes will be the mean (± standard deviation, SD) difference between the two groups for total body (%) (DXA; Lunar Corp., Madison, WI) and regional (e.g., mid-thigh) lean muscle mass (%). Regional muscle mass will be assessed by the measurement of the mid-thigh cross sectional area (cm^2^) which will be measured by a Perpheral Quantitative Computered Tomography (pQCT;XCT 3000, Stratec Medizintechnik GmbH, Pforzheim, Germany). A tomographic slice will be taken 66% proximal from the distal tibia on the right leg, which is considered the largest cross-sectional area of the lower leg [36]. The pQCT results will be analysed using the BoneJ plugin for ImageJ [37]. Measurements for the DXA and pQCT will be taken at familiarisation (week 0), pre-testing (week 1) and post-testing (week 11) and all scans will be carried out by the same researcher (ZH). The outcomes taken over the two consecutive weeks (e.g., familiarisation and baseline) will allow for researchers to report the coefficient of variation (CV) values to report test-retest reliability. For both the pre-testing and post-testing visits participants will be asked to consume 500 ml of water 45–60 min prior to body composition testing to control for hydration status and to minimise the influence hydration status on DXA- derived measure. Confirmation of hydration status will also be carried out via measuring plasma osmolality (Osmomat 3000, Gonotec, Utah, United States of America) from plasma taken from venous blood samples in duplicate.

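### Two outcomes share primary status at two-sided 0.05, with one sample size calculation and no rule for how they combine; if either suffices, the false-positive risk is about 7% to 9.75%

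*Protocol article*

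**What the plan says.** **Two primaries.** The Lean body mass section, under Primary outcomes, uses the plural: "The primary outcomes will be the mean (± standard deviation, SD) difference between the two groups for total body" (by DXA, in %) together with "regional (e.g., mid-thigh) lean muscle mass" (also labelled %). The next sentence says that the regional measure is mid-thigh cross-sectional area by pQCT, in cm². The Objectives section gives both the same standing in the primary aim: "pre- to post-intervention changes in total body and regional lean body mass (e.g., mid-thigh) compared with a placebo condition".

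**One calculation.** The Sample size section has a single calculation: 21 per group, 80% power, α = 0.05, assumed SD 2.2%, "to detect a 2% difference between groups in percentage lean mass change". It mentions neither DXA nor total body nor mid-thigh.

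**One threshold.** The Statistical methods section states: "All tests will be two-tailed with statistical significance set at" p < 0.05. The article gives no order of testing, no division of α, and no rule on whether one or both primary outcomes must be significant.

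**The concern.** With two equally ranked primary outcomes and 0.05 allowed for each, a trial with no true effect has two chances to produce a significant primary result. Unless the plan says how the two combine, the 5% attached to the primary claim is not assured. The Discussion expects the results to inform athletes' and coaches' choice of pain management. A finding on one muscle measure and not the other would be hard to interpret if its status had not been settled beforehand.

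Two further gaps make this harder to settle later. The sized outcome is not identified, so the sample size does not show which of the two was meant to lead. The regional measure is also described inconsistently: a percentage in one sentence and an area in cm² in the next; mid-thigh by name, but with the slice located relative to the distal tibia and described as a lower-leg site.

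**Working it through.** **Inputs from the article.** Difference 2%, SD 2.2%, 21 per group, α = 0.05, power 80%, about 20% dropout, 52 recruited (Sample size); two-sided 0.05 for every test (Statistical methods); two primary outcomes (Lean body mass). The article gives no correlation between the two outcomes, so the correlations below are assumptions.

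**1. The plan's own figure.** Standardised effect = 2/2.2 = 0.909.
- Normal approximation: n per group = 2 × (1.96 + 0.8416)² × (2.2/2)² = 2 × 7.849 × 1.21 = 18.99, so 19 (38 in total).
- Two-sample t-test, as in the Stata command cited: n = 20.0016, rounded up to 21 (42 in total). This reproduces the article.
- Power at 21 per group: noncentrality = 0.909 × √(21/2) = 2.946, giving 82.0% at two-sided 0.05.
- Dropout: 42/0.8 = 52.5, against 52 stated, which is within the approximate 20%.

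The calculation is sound for one outcome tested at the full 0.05.

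**2. Error if either outcome is enough.** For independent tests, 1 − 0.95² = 0.0975. For correlated, jointly normal test statistics, the error is 1 − P(|Z₁| < 1.96 and |Z₂| < 1.96):

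| Assumed correlation | Chance of at least one false positive |
|---|---|
| 0 | 9.75% |
| 0.3 | 9.51% |
| 0.5 | 9.07% |
| 0.7 | 8.35% |
| 0.8 | 7.81% |
| 0.9 | 7.04% |

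The error approaches 5% as the correlation nears 1. For jointly normal statistics 9.75% is the maximum.

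**3. Error under the other possible rules.**
- Both must be significant: the error does not exceed 5%, but power to succeed on both is lower than on one.
- Fixed order, with the second tested only after the first is significant: the error is at most 5%, and each test still uses 0.05.
- α divided equally, 0.025 each: the error is at most 5% (1 − 0.975² = 4.94% if independent). Power at 21 per group falls from 82.0% to 73.0% for the stated effect and SD. Restoring 80% takes 25 per group, so 50 evaluable and 50/0.8 = 62.5, or 63, recruited.

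Of these, a fixed order or a single primary outcome holds 5% for the primary claim without more participants and without loss of power for the leading outcome.

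**The case against.** The strongest reply is that this is a condensed article. Rules for multiplicity and success are often left to the full protocol or the analysis plan, and the Trial status section shows that a numbered protocol lies behind it. The 0.05 sentence is also a general convention, compatible with a fixed order or with a requirement that both succeed, because each of those also tests at 0.05. This stands in part: the article does not state an either-or rule, so the inflated figure is conditional. But the article does more than stay silent. It gives two outcomes equal primary status, fixes 0.05 for all tests and sizes on one unidentified outcome. An unseen plan that divided α would contradict its text.

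Four stronger readings are tempting and are not supported:
- *The error rate is 9.75%.* That needs zero correlation and an either-or rule. The thigh is part of the total-body measure, so positive correlation is likely.
- *The e.g. lets another region be substituted after the data are seen.* The very next sentence names mid-thigh cross-sectional area by pQCT, and so does the Abstract. The real difficulty is the inconsistent definition of that measure.
- *The trial was sized on DXA total-body lean mass and the regional outcome has no power basis.* The Sample size section does not say which outcome it means, and the Lean body mass section labels both in %.
- *There are three primaries, because the Discussion lists mid-thigh area beside regional lean mass.* The Lean body mass section defines the regional outcome as that area, so two is the supported count.

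**Conclusion.** The concern holds in a conditional form. As published, the plan has two primary outcomes, one threshold of 0.05 for every test, one sample size calculation whose outcome is not identified, and no rule for combining the two. If significance on either is taken as a positive primary result, the family-wise error is about 7.0% to 9.75% for assumed correlations of 0.9 to 0.

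This rests on jointly normal test statistics and on correlations that the documents do not supply. The power figures (82.0% and 73.0%) are for an unadjusted t-test. The planned linear models adjust for baseline, sex and SMI, so these are not the power of the planned analysis. The sample size arithmetic itself is correct. The point should be settled before unblinding, but it does not call the design into question.

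**What to change.** Before unblinding:
1. State which outcome the Sample size section refers to. Total-body lean mass by DXA is the natural reading, since the regional measure is an area in cm²; the sponsor should confirm it.
2. Make that outcome the single primary, tested at two-sided 0.05.
3. Make the other outcome one fixed key secondary, tested at 0.05 only if the primary is significant and otherwise reported as supportive.
4. Delete the e.g. in the Objectives and Lean body mass sections, and define the regional measure in one way throughout: its unit (% or cm²) and its anatomical site (mid-thigh, or the lower-leg slice located from the distal tibia).

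**Cost.** Wording only. The 42 evaluable participants and the roughly 82% unadjusted t-test power for the sized outcome are unchanged. The outcome placed second loses stand-alone primary status. If the sponsor prefers to keep two primaries by dividing α, the price is the fall to 73.0% power or the larger sample shown above.
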